### Study Setting and Recruitment

This study does not have a specific physical study site; it focuses on low-income countries that stand to benefit from ETAT+ training. Distribution of the intervention is through the Google Play Store, with initial efforts directed toward physical recruitment in Kenya. Recruitment of study participants will be through three main avenues: (1) remotely, by raising awareness of the Android Google app on social media platforms and online health networks forums every couple of weeks during the study duration to promote voluntary, self-enrolment for use of the training tool; (2) use of snowballing sampling by ETAT+ trainers, previous study participants, and lecturers in medical sciences at local Kenyan universities to suggest that (and encourage) other health workers to self-recruit into the study; and (3) use of a study sample from the purposive selection strategy that will be actively convened once every month, with a unique set of participants to ensure the participant recruitment targets are diverse and met. Snowballing sampling is a type of convenience sampling where a group of people (in our case, already recruited participants) recommend potential participants for the study [28]. The cycle of recommendation of participants for inclusion into the study continues during the study duration. This also serves as an indicator of LIFE intervention adoption. The first avenue includes platforms that are focused on health capacity building in the global south in line with LIFE’s focus on low-income contexts. Avenues 2 and 3 will take place at the following sites: Kenyatta National Hospital - Neonatal Nurse Training Unit; College of Health Sciences, University of Nairobi; Kenya Medical Training College (Nairobi); and Gertrude’s Garden Children’s Hospital Nurse Training School (Nairobi).

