### Intervention

The intervention in this study involves adaptive, personalized, and immediate feedback that is provided while learning through a smartphone-based serious gaming Android app. The content to be learned is based on ETAT+ guidelines, a course that is already offered in nine low-income countries [7,8,10]. The intervention will be available on the Google Play Store where it will be publicly accessible, downloadable, and installable to any compatible android-based mobile device. All study participants will receive a link to the mobile app hosted on the Android Play Store. The LIFE app was designed for Android’s Target SDK 19 as the minimum version of Android supported as of February 2019 (which targets 100% of Android devices) [29]. Given that the intervention has undergone alpha and beta testing on health care providers’ smartphones since October 2017 in Kenya, we are confident of the stability of the app.

The personalized immediate feedback to be given to the experimental group participants is designed to arouse meaningful immersive learning experiences from continuous interaction between the learners and the smartphone-based training [30,31]. This adaptive feedback will be provided to experiment group participants after each incorrect attempt at a learning task with three cascading detail levels based on predicted probability that the learner’s next attempt is going to be correct. The wording of the feedback provided is dependent on the number of incorrect choices the learner had selected and the actual incorrect choices themselves. The control group study participants will receive standardized nonpersonalized immediate feedback after each incorrect attempt at a learning task, with the feedback on the first incorrect attempt asking the learner to retry and the feedback on the second attempt providing a detailed explanation of the correct choices to select.

The LIFE app is a measurement tool; at the end of successful completion of a learning session, the platform provides performance scores based on whether each learner’s response to the learning task was correct on the first attempt.

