### Outcomes

The primary endpoint for both arms of the experiment will be the presence of two complete rounds of learning sessions using LIFE, the former is the pretest round and the latter is the posttest round. Both scores will be converted into percentages. From the pre-post scores, the study’s main outcome—the learning effect size (*d*), [35]—will be calculated as follows:

where the pooled SD is defined as:

The bias adjustment is provided by the formula:

where *n*_*T*
_ is the sample size of the treatment group, *M*_*pre,T*
_ is the pretest mean for the treatment group, *M*_*post,T*
_ is the posttest mean for the treatment group, *SD*_*pre,T*
_ is the SD of means for pretest in the treatment group, *SD*_*post,T*
_ is the SD of means for posttest in the treatment group, *n*_*C*
_ is the sample size of the control group, *M*_*pre,C*
_ is the pretest mean for the control group, *M*_*post,C*
_ is the posttest mean for the control group, *SD*_*pre,C*
_ is the SD of means for pretest in the control group, and *SD*_*post,C*
_ is the SD of means for posttest in the control group.

The effect size from equation from (1) is referred to as *Morris G* [35] and represents the mean difference between the study groups. Because of randomization, this calculation allows to control for pre-existing differences among learners (eg, intelligence quotient level), to estimate treatment effectiveness even when the treatment and control groups are not equivalent, and to consider the variances of both pretest and posttest scores. This contrasts with other forms of effect-size calculation such as Hedges G and Becker D, which only use pretest or pooled variances [35]. In this model, the pretest and posttest variances are assumed to be homogeneous.

Secondary outcomes that will be assessed are time difference between each round of learning sessions, the number of times a learner has encountered a learning task up to the current opportunity (ie, cumulative attempts on learning task per learner), the time spent on each learning task, and the level of feedback provided. These calculations will be performed in Python, version 3.6.8 (Python Software Foundation, Wilmington, DE).

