### Sample Size Calculation

Similar interventions in other subject domains have been found to have an mean effect size of 0.22 (95% CI 0.16-0.27) from a meta-analytic fixed-effects model [24]. To detect an effect size of 0.22 with a two-sided 5% significance level and a power of 80%, a sample size of 83 participants per group, who reach the primary endpoint of the study, is necessary. A sample size calculation for a one-way ANOVA, together with one-sample and paired-sample *t* test analysis using the same effect, power, and significance parameters produce the same required sample size. We anticipate recruiting this number of participants (N=166) in 6 months. The sample size calculation formula is given in the Multimedia Appendix 1.

Based on the alpha and beta tests of the LIFE version, we are assuming a 50% dropout rate of study participants, with drop-out defined as the incomplete or single use of the LIFE smartphone app. We plan to recruit at least 332 participants to account for this dropout rate. To encourage repeated usage of LIFE, participants will receive up to three email reminders from the time they are enrolled into the study, spread over 3 weeks. Demographic data will be collected in the app during its initial use by study participants at the end of the first learning session. Thus, for learners who drop out before completing the first session, or chose not to fill in those data, no demographic data will be available. Logistic regression analyses will be performed on these data to evaluate whether there is a systematic bias caused by attrition of study participants that affects the interaction between the study groups and performance, exposure to previous ETAT+ training, clinical cadre, age of participant, and level of experience. In an effort to ensure participant recruitment is at par with the required study sample size, a monthly target of 30 participants, evaluated at the end of each month, has been set for this study.

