### Statistical Methods and Planned Analysis

For the primary endpoint, we will use the Morris G effect size to analyze the differences among group means in the study population. This will be assessed after the performance from the second round of training through the mobile app has been recorded. Secondary analysis will be conducted using regression analysis, with learning gains as the dependent variable and the aforementioned secondary outcomes as the independent variables, to evaluate their effect on learning gains. Learning gains, defined as the amount the health care providers learned divided by the amount they could have learned [40], will be calculated with the formula given in Equation 8 in Multimedia Appendix 1.

Due to the definition of the primary learning outcome used in this study, the outcome cannot be computed for study participants whose dropout is characterized by the lack of at least two complete learning sessions. Without a postbaseline assessment, “intention-to-treat” analysis cannot be performed for dropout cases unless we impute outcomes, which tends to produce biased estimates [41]. This study will not be able to conduct an intention-to-treat analysis. However, dropout numbers will be reported in relation to those who reached the study’s primary endpoint, and their implications will be discussed with regard to self-regulated self-directed learning [37-39].

Qualitative interviews will be conducted in parallel with the experiment for participants who have reached the primary endpoint and those who drop out. These interviews will be used to explore how self-regulation in learning affected the use of the smartphone-based learning platform and to provide context for interpreting the observed learning outcomes from this study apart from offering evidence for tool validation.

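### As worded, the learning-gains ratio has no value for a perfect pretest and weights losses near the ceiling heavily, which makes it a fragile dependent variable for the secondary regression

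*Protocol article*

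**What the plan says.** Four statements in the protocol article bear on this point.

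- **Score.** The Intervention section says performance scores are "based on whether each learner’s response to the learning task was correct on the first attempt". The Outcomes section adds: "Both scores will be converted into percentages". The number of tasks is not given.
- **Ratio.** Statistical Methods and Planned Analysis states "Learning gains, defined as the amount the health care providers learned divided by the amount they could have learned", and that these gains "will be calculated with the formula given in Equation 8 in Multimedia Appendix 1". That appendix is listed but not shown.
- **Use of the ratio.** The same section says: "Secondary analysis will be conducted using regression analysis, with learning gains as the dependent variable". The independent variables are the secondary outcomes: time between rounds, cumulative attempts, time on task and feedback level.
- **Primary analysis.** This is separate: "we will use the Morris G effect size to analyze the differences among group means in the study population".

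On who may enter, Eligibility Criteria admits both practising staff and those in training, and has no exclusion for earlier ETAT+ training. Recruitment includes "use of snowballing sampling by ETAT+ trainers, previous study participants, and lecturers in medical sciences". The attrition analysis described under Sample Size Calculation lists "exposure to previous ETAT+ training, clinical cadre, age of participant, and level of experience".

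**The concern.** A ratio of gain to remaining headroom behaves badly when the headroom is small. With scores capped at 100%, a learner who starts at 100% has a zero denominator and no value. A learner who starts just below 100% and slips has a small loss divided by a very small number. The same slip in a mid-range learner gives a small negative value.

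Two consequences follow for the secondary regression. Learners with a perfect pretest drop out of it because of their own score, on top of those already lost for not completing two rounds. In addition, a handful of near-ceiling learners can hold much of the variance of the dependent variable, so ordinary slips on one or two tasks could weigh heavily on the coefficients for time, attempts and feedback level. The article's text states no rule for either case.

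**Working it through.** The plan gives no range, SD or count for learning gains, so there is no figure to reproduce. The check evaluates the stated definition and then sizes it under assumptions.

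**1. Formula.** Amount learned = post - pre. Amount that could have been learned = 100 - pre, taking 100% as the maximum. Hence g = (post - pre)/(100 - pre). This is a reading of the sentence; Equation 8 itself is not available.

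**2. Direct evaluation.**

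| Pre | Post | g |
|---|---|---|
| 0 | 100 | 100/100 = +100% |
| 50 | 40 | -10/50 = -20% |
| 95 | 85 | -10/5 = -200% |
| 95 | 75 | -20/5 = -400% |
| 100 | any | denominator 0, no value |

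**3. Limits.** The maximum is +100%. With J equally weighted tasks, the smallest non-zero headroom is one task. The minimum occurs when a learner with J - 1 tasks correct then gets none: g = -(J - 1)/1. For J = 10, 20 and 40 this is -900%, -1,900% and -3,900%. The lower limit is finite but far larger in size than the upper one.

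**4. Size under assumptions.** None of these inputs is in the article: 20 or 30 right-or-wrong tasks; ability normal on the logit scale with SD 0.8 and mean 0.4, 0.85 or 1.4 (mean pretest about 59%, 68% or 78%); and a true gain of 0.8 logit for every learner. With 200,000 simulated learners per setting:

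- No value (pretest 100%): 0.2% to 5.8%. For the 166 planned completers this is 0.002 x 166 = 0.3 to 0.058 x 166 = 9.6 learners.
- Negative g although every true gain is positive: about 7% to 10%.
- Strictly below -100%: 0.4% to 1.8% of learners with a value, or about 0.004 x 166 = 0.7 to 0.018 x 166 = 3.0 learners. They carry about 28% to 40% of the variance of g; the lower end moves by a point or two between simulation runs.

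**5. A different model.** This one used beta-distributed ability with concentration 8, 25% of the remaining gap learned, 10, 20 or 40 tasks, and mean pretest 50% to 90%. With 20 tasks and a mean pretest of 65%, about 3 of 166 learners have no value. The 10% of evaluable learners with a pretest of at least 90% carry about 60% of the variance (SD 0.61 with them, 0.40 without). Across all settings, learners without a value range from about 0 (40 tasks, mean 50%) to about 82 of 166 (10 tasks, mean 90%). The direction is stable, but the size depends strongly on inputs the article does not give.

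**6. A bounded form for comparison.** Gains are divided by (100 - pre) and losses by pre. Then 95 to 75 gives -20/95 = -21% instead of -400%, 95 to 0 gives -100% instead of -1,900%, and 100 to 90 gives -10% instead of no value. Only 100 to 100 still needs a stated rule.

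**The case against.** The strongest objection is that the operative formula is Equation 8, which is not shown. It may already treat falling scores and perfect pretests separately, and an article may leave such detail to its appendix. This stands as a limit: the defect cannot be confirmed for the formula that will be run. It does not remove the point, because the article itself defines the quantity. If Equation 8 departs from that definition for some learners, the text should say so.

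A reader might also infer stronger versions that the documents do not support.

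- **That near-ceiling pretests are to be expected.** ETAT+ trainers are described as encouraging others to join, not as participants. Earlier ETAT+ exposure is only a variable in the attrition analysis, with no prevalence given. The Introduction says that few providers have the basic newborn resuscitation training, and the named sites are largely training institutions. High pretests are plausible, no more.
- **That losses are unlimited.** They are bounded at -(J - 1) x 100%.
- **That the regression would mainly describe noise.** No regression result was shown to be dominated in this way. In the logit-model settings the extreme values carry less than half of the variance.
- **That the primary comparison is compromised**, because the hypothesis in Objectives is worded in learning gains. The primary analysis is assigned to Morris G, which uses group means and SDs and has no individual headroom denominator.

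Finally, a gain relative to headroom is a deliberate choice with a cited source, and a regression of posttest on pretest answers a somewhat different question and has its own compression at the ceiling. That is fair, and it is why the ratio may stay as a descriptive measure in bounded form.

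**Conclusion.** The point holds for the definition as the article words it. The zero denominator at a 100% pretest and the asymmetry between gains and losses follow from that wording and need no distributional assumption. How much they matter does depend on assumptions. With 20 or 30 tasks and a mean pretest of 59% to 78%, up to about 6% of learners have no value, and fewer than 2% carry roughly three to four tenths of the variance. With easier or shorter content the loss could be much larger; with harder or longer content it could be negligible. The weakness is confined to the secondary regression and is conditional on Equation 8 not already dealing with these learners. It is a worthwhile, inexpensive improvement and not a flaw in the trial's main comparison.

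**What to change.** In the secondary regression, replace the ratio with the posttest percentage as dependent variable and add the pretest percentage as a covariate; the planned independent variables stay as they are. Every learner with two complete rounds then has a value.

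If a normalised gain is kept for description, define it in a bounded form: gains divided by (100 - pre), losses divided by pre, and 100 to 100 scored as 0. Report the number of learners with a 100% pretest by arm.

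If Equation 8 already covers perfect pretests and falling scores, state that rule in the text.

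The cost is one or two sentences and no new data. The article describes the full analysis as still to come, so the rule can be fixed beforehand. The small downside is less direct comparability with education studies that use the ratio.

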**Results:**

This project was funded in November 2016. It has been approved by the Central University Research Ethics Committee of the University of Oxford and the Scientific and Ethics Review Unit of the Kenya Medical Research Institute. Recruitment and data collection began from February 2019 and will continue up to July 31, 2019. As of July 18, 2019, we enrolled 541 participants, of whom 238 reached the primary endpoint, with a further 19 qualitative interviews conducted to support evaluation. Full analysis will be conducted once we reach the end of the study recruitment period.

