## Methods

### Study Design

The study (trial registration: Pan African Clinical Trials Registry PACTR201901783811130) will have a parallel-group double-blinded randomized experiment design with an allocation ratio of 1:1. The participants will be randomized to the intervention or control group when they launch the android-based training app for the first time on their individual smartphone devices.

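### The only primary contrast is an unadjusted completers-only effect size, defended by ruling out intention-to-treat and calling imputation biased, although completion follows randomization and arm-specific feedback

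*Protocol article*

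**What the plan says.** Under Statistical Methods and Planned Analysis, the protocol article says that "the outcome cannot be computed for study participants whose dropout is characterized by the lack of at least two complete learning sessions". It goes on that an intention-to-treat "analysis cannot be performed for dropout cases unless we impute outcomes, which tends to produce biased estimates", and closes the matter: "This study will not be able to conduct an intention-to-treat analysis".

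Three other sections fix the order of events.
- **Study Design:** "The participants will be randomized to the intervention or control group when they launch the android-based training app for the first time".
- **Intervention:** "This adaptive feedback will be provided to experiment group participants after each incorrect attempt at a learning task". Control learners receive standardized feedback at the same points, so the arms differ from within round 1.
- **Outcomes:** the endpoint is having two complete rounds. Morris G is built from the pretest and posttest means of each arm, and randomization is cited as the reason why it controls for pre-existing differences between learners.

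Sample Size Calculation assumes 50% dropout and plans logistic regressions to look for systematic bias from attrition. The analysis section adds that dropout numbers will be reported and that dropouts as well as completers will be interviewed. The abstract's Results give the count on 18 July 2019: "we enrolled 541 participants, of whom 238 reached the primary endpoint".

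**The concern.** Completing a second round happens after allocation and after exposure to the allocated feedback. If the feedback affects who carries on, completers in the two arms need not be comparable, and the protection of randomization that the Outcomes section relies on is not assured.

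The stated reason does not repair this. An imputation can be biased if its assumptions fail, but so can an analysis that drops the same learners. Rejecting one does not validate the other.

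The statement of impossibility is also too broad. A learner who used the app for one complete session counts as a dropout but has a round-1 score. Whether a learner reached two rounds is known for everyone randomized.

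At stake is whether a difference near the target of 0.22 can be read as an effect of adaptive feedback or could be produced by selective completion.

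**Working it through.** **1. The plan's own dropout figure.** Inputs from Sample Size Calculation: 83 completers per group and 50% dropout. 2 × 83 = 166, and 166 / (1 − 0.50) = 332. This matches the stated recruitment target, so the plan knowingly accepts excluding half of those recruited.

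**2. Non-completion to date.** From the abstract: 541 enrolled, 238 at the endpoint. 541 − 238 = 303, and 303/541 = 56.0% (95% Wilson interval 51.8% to 60.1%). The contrast would use 238/541 = 44.0% of those enrolled.

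**3. What the completer result leaves open.** Suppose completers show the target of 0.22 SD.
- If non-completers would have shown no difference, the effect in all enrolled is 0.22 × 0.440 = 0.097 SD.
- The overall effect is zero if the difference among non-completers is −0.22 × 238/303 = −0.17 SD.

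**4. Illustration of bias under a true null.** The documents give neither completion by arm nor the pre-post correlation, so these are assumptions: pretest and posttest with SD 1 and correlation ρ; n = 541; completion log-odds of −0.24 in the adaptive arm, regardless of pretest, and −0.24 + 0.5 × pretest in the control arm.

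Under these assumptions, simulation puts the mean pretest of completers at about 0.26 SD in the control arm and 0 in the adaptive arm. Expected change given pretest is (ρ − 1) × pretest, so the spurious contrast is (1 − ρ) × 0.26.

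| ρ | (1 − ρ) × 0.26 | Simulated bias, change score | Rejection at nominal 5% |
|---|---|---|---|
| 0.3 | 0.18 | 0.18 | about 23% |
| 0.5 | 0.13 | 0.13 | about 17% |
| 0.7 | 0.08 | 0.08 | about 12% |

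Completion was about 44% in both arms, so a report of dropout numbers by arm would have shown nothing unusual.

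**5. Two variations that limit the claim.**
- *Same completers, adjusted for pretest:* bias is about 0 and rejection about 5%.
- *Same slope of 0.5 in both arms, unadjusted change score:* bias is about 0 and rejection about 5%.

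The bias in step 4 thus needs selection that differs by arm combined with a contrast that does not condition on pretest.

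**6. Is imputation the biased option?** In a second null simulation (ρ = 0.6), completion depended on pretest in opposite directions by arm (slopes ±0.8) and about 45% completed. The completers' gain difference averaged −0.31 SD. Imputing the posttest from the pretest within arm gave −0.004 SD. Under missing-at-random given pretest, the plan's ranking is reversed.

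**The case against.** The strongest reply is that the simulation faults the unadjusted change score, not the restriction to completers. That stands: step 5 shows that pretest adjustment in the same completers removes the bias, and that equal selection in both arms causes none. A reader might infer that dropping non-completers is biased in itself, or always needs a stronger assumption than imputation. The documents and calculations do not support that. With one posttest and missingness depending on pretest, a pretest-adjusted completer analysis needs essentially the same assumption as imputation from pretest. But the plan's primary contrast is the unadjusted one.

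A reader might also infer that 56% of learners are lost, or lost unequally. The count was taken while recruitment was open until 31 July and reminders were still running, and it may include people excluded later, such as those in high-income countries. No split by arm is given, so differential attrition is a possibility and not an observation.

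Nor can everyone randomized simply be modelled. The app is public, while eligibility depends on professional cadre, and demographic data come only at the end of the first session. For learners who leave earlier, neither eligibility nor a full round-1 score is established. This limits the remedy.

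The plan does look at attrition, through logistic regression, dropout counts and interviews, and it words the imputation remark as a tendency, citing a source not available here. These measures diagnose. None of them changes the estimate, and the regression lacks the learners without demographic data.

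**Conclusion.** The point holds in a limited form. The plan fixes an unadjusted completers-only Morris G as its sole primary contrast and defends it with two statements that do not carry the weight: that no intention-to-treat analysis is possible, and that imputation is the biased choice. Completion is a post-randomization event that the allocated feedback can influence, and about half of learners are excluded (50% planned, 56% at the interim count).

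If completion depends on pretest differently by arm, the contrast can be off by about 0.08 to 0.18 SD with no true effect, against a target of 0.22. This rests on an assumed log-odds slope of 0.5 per SD in one arm only and pre-post correlations of 0.3 to 0.7. It shows what could happen. Neither the size nor the direction of any actual bias can be derived from the documents.

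It would also go too far to conclude that a missing-at-random model cures the problem. It deals with selection on the observed round-1 score. Selection on unobserved gain remains under any such model and can only be explored by sensitivity analysis.

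**What to change.** 1. Delete the claims that imputation is the biased option and that no analysis of all randomized learners is possible. State which learners can be included and under what assumption.
2. Estimate the effect with a model that conditions on the round-1 score and uses all eligible randomized learners with a recorded round 1, by likelihood or multiple imputation under missing-at-random. Report it alongside the completers' Morris G.
3. Add a delta-adjusted tipping-point analysis that shifts the missing round-2 scores separately by arm, and report the shift at which the conclusion changes.
4. Compare the proportion reaching two rounds between arms among all randomized learners. State that eligibility cannot be verified for those who left before completing session 1.

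Keep the planned attrition regressions, dropout counts and interviews as supporting description.

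The cost is protocol wording and modest extra analysis of scores that the app already records; no new data collection is needed. The article places the full analysis in the future, so the change can still be made beforehand. The price is explicit reliance on missing-at-random, which the tipping-point analysis examines but does not remove. Feedback also operates during round 1, so treating that score as a baseline is itself an assumption to state; scoring on first attempts limits the problem but does not exclude it.
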